### Intervention Program

The health care program is a proactive, blended, and integrated care program offered by a physical therapist and mental health nurse. The program will start with a physical approach since patients’ perception of the symptoms usually has a somatic focus and MUPS patients are often reluctant to accept psychological oriented treatments [23,24]. The aim of the health care program is to reduce complaints of moderate MUPS, stimulate self-management, and prevent chronic MUPS. The health care program is focused on patients’ insight, perception of symptoms, and modifiable prognostic risk factors for the development of chronic MUPS, using a cognitive behavioral approach and therapeutic neuroscience education as well as encouraging self-management and an active lifestyle using graded activity (details are provided in Multimedia Appendix 1). It consists of 3 steps and the face-to-face sessions will be integrated with eHealth modules, called blended health care. The content of the eHealth modules will be discussed during the face-to-face sessions. Details of the 3 steps are listed below:

Intake: The program will start with an intake session with both the physical therapist and the mental health nurse. During the intake session the complaints, treatment goals, treatment demand, and perpetuating factors of the patient will be identified according to the somatic, cognitive, emotional, behavioral, and social factors (SCEGS) model [3]. After the intake the physical therapist and mental health nurse discuss the complaints, treatment goals, and treatment demand.The physical therapist will focus on the somatic complaints (ie, physical symptoms, duration and course of symptoms, severity of symptoms, and physical functioning) and will conduct a physical examination to get insight to factors that are related to the content of the health care program (eg, posture and movement, breathing patterns, and muscle tension) and to determine if symptom specific exercises are needed.The mental health nurse will focus on cognitive, emotional, behavioral and social complaints.Face-to-face sessions:Patients will have 4 face-to-face sessions with the physical therapist (week 1, week 3, week 6 and week 12) where the focus will be on the perception and acceptation of physical complaints of the patients. The physical therapist will start with education regarding the unexplained symptoms. Therapeutic neuroscience education according to the sensitization model is of particular interest due to patient’s somatic fixation and anxiety for a severe disease [17]. Concurrently, graded activity will be used to gradually expand activities performed by the patient using principles of operant conditioning [25,26]. The graded activity schedule can be performed in daily life. In week 6, the physical therapist will discuss the patients’ lifestyle (eg, exercise, sleep, and relaxation) with the focus on behavioral changes to promote a healthy lifestyle. In week 12, the physical therapist will discuss long-term goals as well as how patients can maintain a physically active lifestyle.Patients will have 3 face-to-face sessions with the mental health nurse (week 1, week 3, and week 6). In all 3 face-to-face sessions the mental health nurse will train coping strategies according to perpetuating factors and operant conditioning [25], with the focus on changing perception and acceptation. The mental health nurse will start with education regarding general perpetuating factors with the link to possible perpetuating factors of the patient. In the next 2 face-to-face sessions, the link between the perpetuating factors and patients coping strategies will be made, with the focus on behavioral change.eHealth modules: The Web-based part of the health care program consists of exercises (instruction videos) and information modules on self-management and educative themes (description and videos). The modules consist of 3 components which are listed below.Graded activity, an activity-focused method with operant conditioning behavioral principles with 3 consecutive phases. In the starting phase, the patient will choose an activity they want to expand gradually. The patient will perform the chosen activity to their tolerance level (ie, until pain or fatigue drives them to stop; this will be pain-contingent) while their performance is recorded in distance units, time, or number of repetitions. After at least 3 pain-contingent measurements, occurring over several days, a baseline will be determined, and the patient sets his or her individual treatment goal. In the treatment phase, the chosen activity will be increased gradually (ie, time-contingent) and an individual scheme will be drawn up. In the integration phase, patients will be stimulated to adhere to the activity in their daily living [25,26]Videos of prescribed home exercises by their physical therapistVideos and information on self-management and educational themes such as central sensitization, perpetuating factors, graded activity, behavioral change, stress, coping, relaxation, lifestyle advice, creating and performing an exercise plan, and avoiding a relapse.

### Usual Care

Patients in the control health care centers will get care as per usual without any restrictions. This care could include care of the GP, physical therapist, mental health nurse, and psychologist.

### Outcomes

#### Primary Outcome

The primary outcome measures are impact of symptoms and quality of life.

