**Figure 1 figure1:**
[figure not shown]
PRESUME screening method.

The primary objective of the present study is to investigate the effectiveness of the proactive, blended and integrated mental health and physical therapy care program (PARASOL) on impact of symptoms, as well as the physical and mental dimensions of quality of life in patients with moderate MUPS in comparison with usual care. Secondary objectives are to study the effect on severity of (psychosocial) symptoms, general health, physical behavior, illness perception, and self-efficacy in patients with moderate MUPS as well as to determine the cost-effectiveness of this program.

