#### Measurements

Three time points (baseline, 3-month, and 12-month follow-up) will be used for data collection. In addition, cost questionnaires will also be sent to the patients at 6 and 9 months. Furthermore, the impact of symptoms will be measured weekly between 0 and 3 months, followed by monthly measurements between 6 and 12 months. We offer no financial incentives to complete questionnaires or to carry the Acitv8 activity monitor. The measures that will be collected are listed below and Table 1 gives a summary of all measures that will be collected.

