Impact of symptoms, which addresses adequate relief using a validated single question, which is scored on a dichotomous scale (“Over the past week have you had adequate relief of your symptoms?”) [27,28]. A responder for adequate short-term relief is defined as a patient who will report adequate relief of their symptoms for at least six of the twelve weeks between the baseline and three-month follow-up. In addition, a responder for adequate long-term relief will report adequate relief of their symptoms for at least three of the six months between the 6- and 12-month follow-up. Otherwise, a patient will be defined as a nonresponder. Adequate relief is a validated clinically relevant endpoint and is defined at the point where the individual patient is satisfied with treatment [29].Quality of life will be measured with the 36-Item Short Form Health Survey (RAND-36) health survey. The RAND-36 is a valid and reliable self-reported questionnaire [30]. The questionnaire consists of eight subscales, namely physical functioning, social functioning, role-physical or emotional problems, mental health, vitality, bodily pain, and general health. A higher score on the scale of 0-100 indicates a better quality of life [30,31].Severity of symptoms, defined as self-perceived pain and fatigue in the past week, will be measured with an 11-point numeric scale (score 0-10) [32].Severity of psychosocial symptoms will be measured with the Four-Dimensional Symptom Questionnaire (4DSQ) questionnaire. This questionnaire consists of 4 subscales, namely distress, depression, anxiety, and somatization [33,34].Self-perceived health will be measured with the EuroQol-5D (EQ5D) questionnaire. This questionnaire will measure the perceived health on five levels (ie, mobility, self-care, usual activities, pain/discomfort, and anxiety/depression) [35].Physical movement behavior will be measured with the Activ8 activity monitor [36]. The Activ8 is a validated activity monitor to measure physical behavior by measuring several activities and postures (lying, sitting, standing, walking, running, and cycling). Patients will wear the Activ8 activity monitor for 1 week at varying intervals during the study. They will wear it at baseline, at 3 months follow-up, and at 12 months follow-up.Illness perceptions will be measured using the Brief Illness Perception Questionnaire. This questionnaire is an eight-item scale designed to assess cognitive and emotional representations of illness on an ordinal scale (0-10) [37,38].Self-efficacy will be measured with the Hei-Q questionnaire, which is a user friendly, valid, and reliable questionnaire specifically developed to evaluate patients’ education and self-management programs for patients with chronic complaints [39].Health care use and indirect costs through illness and absenteeism will be measured with Trimbos/iMTA Questionnaire for Costs associated with Psychiatric Illness (TIC-P) questionnaire to evaluate the cost-effectiveness of the program in terms of costs per Quality Adjusted Life Years (QALYs) [40]. Patients will be asked to complete the cost questionnaire every 3 months, since this questionnaire focuses on health-related costs in the past 3 months. QALYs will be measured using the EQ-5D scores [41]. In this way, we will get information of patients’ healthcare utilization and (unpaid) productivity losses.Besides the above parameters, the efficacy, barriers, and facilitators of the Web-based component of the blended PARASOL intervention from a patient’s perspective will be measured using the System Usability Scale (SUS). The SUS will be completed by patients of the intervention group at the end of the health care program (3-month follow-up). The questionnaire will measure the perceived usability by ten statements which can be scored on a 5-point Likert scale (‘totally agree’ to ‘totally disagree’). The SUS is a simple, valid, and reliable measurement and is often used the evaluate the usability of eHealth applications [42].

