### Sample Size

The number of eligible patients was calculated according to Campbell et al for cluster randomized trials [43]. The power calculation is based on an intracluster correlation coefficient of 0.04 [44,45] and a minimum of 20 patients per health care center. Additionally, we assume a minimal clinical detectable change of >10 points in the sum score of physical functioning of the RAND-36 questionnaire, and a SD of 23.8 [10]. Based on these assumptions and a power of 80% (alpha=.05), at least ten health care centers and 206 participating patients are needed. With an expected drop-out rate of 20%, a total of 248 participating patients (124 patients per arm) are needed for the study.

**Table 1 table1:** Summary of measures to be collected.

Outcome measures		Data collection instrument	Follow-up measurements				
			Baseline	3 months	6 months	9 months	12 months

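### The primary outcome is not fixed to one score and time point, power is given for one RAND-36 score only, and the article does not say what counts as success

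*Protocol article*

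**What the plan says.** Four parts of the Protocol article bear on the primary outcome.

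- **Primary Outcome** names two domains and nothing narrower: "The primary outcome measures are impact of symptoms and quality of life".
- **Introduction, primary objective** names three targets: "impact of symptoms, as well as the physical and mental dimensions of quality of life".
- **Measurements** describes the RAND-36 as an instrument ("The questionnaire consists of eight subscales") without singling out a score. It defines two binary relief endpoints. The short-term one begins "A responder for adequate short-term relief is defined as a patient who will report adequate relief of their symptoms for at least six" and counts 12 weeks. For the other, "a responder for adequate long-term relief will report adequate relief of their symptoms for at least three of the six months" between months 6 and 12. On timing: "Three time points (baseline, 3-month, and 12-month follow-up) will be used for data collection". Table 1 lists both primary domains at 3 and 12 months and marks neither visit as primary.
- **Sample Size** assumes "a minimal clinical detectable change of >10 points in the sum score of physical functioning of the RAND-36 questionnaire", with SD 23.8, ICC 0.04, at least 20 patients per center, 80% power and alpha .05. The result is 206 patients, raised to 248 for drop-out. No responder rate, difference or power is given for relief or for mental quality of life.

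The Statistical Analysis section specifies longitudinal mixed analyses. It gives no test level per outcome and no rule for combining the primaries.

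**The concern.** The sections that should identify the same primary quantity stop at different levels: a domain, its two dimensions, and one physical score. Relief has two endpoints and the RAND-36 has two follow-up visits, with no choice made between them. A reader of the eventual report could not tell from this article which result decides the trial.

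That leaves two open questions. If a favorable result on any primary quantity may be called a positive trial, the overall false-positive risk exceeds the stated .05. If both domains must be favorable, the error rate is protected, but the chance of success depends on an outcome for which no power was calculated. The 80% power statement covers neither case.

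**Working it through.** **1. The article's own sample size.** Inputs from Sample Size: difference 10, SD 23.8, power 80%, alpha .05 (two-sided assumed), ICC 0.04, 20 per center.

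- Without clustering: n per arm = 2 × [23.8 × (1.960 + 0.842) / 10]² = 88.9, so 89.
- Design effect: 1 + (20 − 1) × 0.04 = 1.76.
- With clustering: 89 × 1.76 = 156.6, so 157 per arm and 314 evaluable. The stated 206 is not reproduced. One-sided .05 gives about 250.
- Drop-out: 206 × 1.2 = 247.2, which matches 248. A 20% loss from 248 leaves 248 × 0.8 = 198.

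**2. Power for physical functioning at the stated size.** SE = 23.8 × √(4 × design effect / N); power = Φ(10/SE − critical value).

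| Evaluable | Per center | Design effect | SE | Power at .05 | Power at .025 |
|---|---|---|---|---|---|
| 206 | 20 | 1.76 | 4.40 | 62% | 51% |
| 198 | 13.2 (15 centers) | 1.49 | 4.13 | 68% | 57% |

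These use the normal approximation. A t reference with degrees of freedom from the number of centers lowers the .05 figures to about 51% (206 in 10 centers) and 61% (198 in 15 centers).

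**3. Error if any one test at .05 were enough (conditional).** For k independent tests the familywise error is 1 − 0.95^k. Correlated values are from simulation of equally correlated test statistics.

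| Tests | Independent | r = 0.3 | r = 0.5 | r = 0.7 |
|---|---|---|---|---|
| 2 (one per domain) | 9.8% | 9.5% | 9.1% | 8.3% |
| 6 (relief in two windows; two dimensions at two visits) | 26.5% | 24% | 21% | 16% |

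**4. If both domains must succeed.** Familywise error stays at or below .05. Joint power cannot exceed the smaller of the two single-outcome powers, so it is at most about 62-68% under step 2. Its actual value is unknown because relief has no stated rate or effect.

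**5. Detectable relief difference.** Inputs: 198 evaluable (99 per arm), ICC 0.04 and two-sided .05. Control rates of 20-40% are assumed, since the article gives none.

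- 13.2 per center: effective n = 99 / 1.49 = about 66.5 per arm; 80% power needs about 22-24 percentage points.
- 20 per center: effective n = 99 / 1.76 = 56.25 per arm; 80% power needs about 24-26 percentage points.

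With 206 evaluable, 20 per center and control rates of 20-50%, power for a 10-point difference is only 19-24%.

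**The case against.** The strongest reply is that the sections are nested, not rival: a domain, its dimensions, and a physical score inside that domain. On this view the trial is sized on part of a named primary, and short-term and long-term relief are openly labeled as separate questions. Testing order is also commonly left to an analysis plan, which is not shown. Much of this stands. Physical functioning does belong to a named primary, and the lack of a detailed testing hierarchy in a journal article would not be a finding by itself. But a testing rule needs named tests to act on, and the dedicated outcome, measurement and sample-size sections do not agree on what those are.

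A reader might infer that each score and visit is tested at .05 and that any one success suffices. The document does not say so. Alpha .05 appears only in the power calculation, the primaries are joined by the word *and*, and a mixed model could yield one overall effect per outcome. A reader might also count eight subscales at two visits plus two relief windows, 18 tests, and quote 60% familywise error. That treats a description of the questionnaire as a list of primaries and assumes independence; at correlation 0.5 the figure is about 40%, and no section makes the subscales separate primaries.

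Finally, inclusion began in March 2017 and the trial is unblinded, so dropping a published primary domain now would invite a charge of outcome switching. That stands, and it is why the fix keeps both domains.

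**Conclusion.** The point holds in this form: the primary is not tied to one score and one time point, only one component has a power calculation, and the success criterion is unstated. It is not established that the trial will run at an inflated error rate. The figures of 8-10% (two tests) and 16-26% (six tests) apply only if any single test at .05 counts as success. Under a both-must-succeed rule the cost is in power, which is unknown and capped at about 62-68%.

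The stated 80% for physical functioning does not follow from the article's inputs. An adjustment for baseline with a correlation near 0.59 would bring the requirement down to about 206, but none is mentioned. The relief figures rest on assumed control rates and on applying the same ICC to a binary outcome. Physical functioning is also ambiguous as worded: it could be the subscale or a physical summary score.

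**What to change.** Before any outcome analysis:

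1. Keep both published primary domains and fix one quantity for each: the RAND-36 physical functioning score used in the sample size, stating whether it is the subscale or a summary score, at one named time point; and one of the two relief responder definitions.
2. Test the two by Holm at overall two-sided .05, or state that both must succeed.
3. Make the other RAND-36 scores, the other time point and the other relief definition secondary, and align the objective, Primary Outcome and Sample Size sections.
4. State the detectable relief difference with its assumed control rate (roughly 22-26 percentage points on the assumptions above).
5. Restate the power for physical functioning: about 62% at 206 evaluable with 20 per center, about 68% with 198 over 15 centers, and 51% or 57% at the first Holm step. If baseline adjustment is meant to recover power, say so and give the assumed correlation.

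Cost: wording, a recalculation, and a dated, documented registry update because inclusion has begun. Each primary outcome has somewhat lower power than if tested alone at .05. Holm limits this, because the second test returns to .05 once the first succeeds.

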#### Secondary Outcomes

Several secondary parameters will be measured to determine the influence of the blended e-Exercise health care program on severity of physical and psychosocial symptoms, general health, physical behavior, illness perceptions, self-efficacy, and cost-effectiveness.

#### Measurements

Three time points (baseline, 3-month, and 12-month follow-up) will be used for data collection. In addition, cost questionnaires will also be sent to the patients at 6 and 9 months. Furthermore, the impact of symptoms will be measured weekly between 0 and 3 months, followed by monthly measurements between 6 and 12 months. We offer no financial incentives to complete questionnaires or to carry the Acitv8 activity monitor. The measures that will be collected are listed below and Table 1 gives a summary of all measures that will be collected.

Impact of symptoms, which addresses adequate relief using a validated single question, which is scored on a dichotomous scale (“Over the past week have you had adequate relief of your symptoms?”) [27,28]. A responder for adequate short-term relief is defined as a patient who will report adequate relief of their symptoms for at least six of the twelve weeks between the baseline and three-month follow-up. In addition, a responder for adequate long-term relief will report adequate relief of their symptoms for at least three of the six months between the 6- and 12-month follow-up. Otherwise, a patient will be defined as a nonresponder. Adequate relief is a validated clinically relevant endpoint and is defined at the point where the individual patient is satisfied with treatment [29].Quality of life will be measured with the 36-Item Short Form Health Survey (RAND-36) health survey. The RAND-36 is a valid and reliable self-reported questionnaire [30]. The questionnaire consists of eight subscales, namely physical functioning, social functioning, role-physical or emotional problems, mental health, vitality, bodily pain, and general health. A higher score on the scale of 0-100 indicates a better quality of life [30,31].Severity of symptoms, defined as self-perceived pain and fatigue in the past week, will be measured with an 11-point numeric scale (score 0-10) [32].Severity of psychosocial symptoms will be measured with the Four-Dimensional Symptom Questionnaire (4DSQ) questionnaire. This questionnaire consists of 4 subscales, namely distress, depression, anxiety, and somatization [33,34].Self-perceived health will be measured with the EuroQol-5D (EQ5D) questionnaire. This questionnaire will measure the perceived health on five levels (ie, mobility, self-care, usual activities, pain/discomfort, and anxiety/depression) [35].Physical movement behavior will be measured with the Activ8 activity monitor [36]. The Activ8 is a validated activity monitor to measure physical behavior by measuring several activities and postures (lying, sitting, standing, walking, running, and cycling). Patients will wear the Activ8 activity monitor for 1 week at varying intervals during the study. They will wear it at baseline, at 3 months follow-up, and at 12 months follow-up.Illness perceptions will be measured using the Brief Illness Perception Questionnaire. This questionnaire is an eight-item scale designed to assess cognitive and emotional representations of illness on an ordinal scale (0-10) [37,38].Self-efficacy will be measured with the Hei-Q questionnaire, which is a user friendly, valid, and reliable questionnaire specifically developed to evaluate patients’ education and self-management programs for patients with chronic complaints [39].Health care use and indirect costs through illness and absenteeism will be measured with Trimbos/iMTA Questionnaire for Costs associated with Psychiatric Illness (TIC-P) questionnaire to evaluate the cost-effectiveness of the program in terms of costs per Quality Adjusted Life Years (QALYs) [40]. Patients will be asked to complete the cost questionnaire every 3 months, since this questionnaire focuses on health-related costs in the past 3 months. QALYs will be measured using the EQ-5D scores [41]. In this way, we will get information of patients’ healthcare utilization and (unpaid) productivity losses.Besides the above parameters, the efficacy, barriers, and facilitators of the Web-based component of the blended PARASOL intervention from a patient’s perspective will be measured using the System Usability Scale (SUS). The SUS will be completed by patients of the intervention group at the end of the health care program (3-month follow-up). The questionnaire will measure the perceived usability by ten statements which can be scored on a 5-point Likert scale (‘totally agree’ to ‘totally disagree’). The SUS is a simple, valid, and reliable measurement and is often used the evaluate the usability of eHealth applications [42].
